## Research hypotheses

The proposed experiment will assess if pre-exposure session spacing and pre-exposure in multiple contexts potentiate changes in expected relevance and visual attention to the pre-exposed stimulus, and LI of dental fear. Pain sensitivity will also be measured to test if this variable moderates the influence of the proposed mediators on LI.

### Hypothesis 1

Spaced pre-exposure sessions, compared to no spacing, will (a) increase engagement of the proposed mechanisms (expected relevance and attention), and (b) enhance LI of conditioned fear acquisition, recall, and retention.

### Hypothesis 2

Multiple context pre-exposure, as compared to pre-exposure in a single context, will (a) lead to stronger engagement of the proposed mechanisms (expected relevance and attention), and (b) enhance LI of conditioned fear acquisition, recall, and retention.

### Hypothesis 3

Greater pain sensitivity will be associated with increased engagement of the proposed mechanisms of expected relevance and attention and increased LI.

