#### Moderator variables: pain sensitivity

We will assess *pain sensitivity* through self-report and a behavioral task. Self-reported pain sensitivity will be obtained with the Fear of Pain Questionnaire III [33] in individuals 18 years of age or older and with the Fear of Pain Questionnaire, Child report, in individuals from 6 to 17 years old [34]. Participants will complete the cold pressor test to provide a behavioral indicator of pain sensitivity [35].

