For Hypotheses 1a and 2a, changes expected in the proposed mediators should first be detected in the pre-exposure phase. To test these two hypotheses during the pre-exposure phase, a two-factor repeated measures MANOVA with one-between (pre-exposure group) and one-within-subjects (trial) factor will be run separately for the expected relevance and attention variables. A significant group × trial interaction indicates that mean responses across trials is not the same per group. If the interaction is present, follow-up analyses will focus on examining the plots of the mean change for each group and testing the degree to which the mean change from first to last trial differs between groups. For the conditioning phase, we will conduct a three-way repeated measures MANOVA separately for the two proposed mechanisms. For these models, pre-exposure groups will serve as the between-subjects factor with stimulus and trial being the within-subject factors, and the model will assess the main effects of each variable, as well as all-two-way and three-way interactions. Follow-up analyses depend on the nature of effects that are present (e.g., type of interactions or main effects). We anticipate differences will be larger between pre-exposure groups—predominantly at the early trials for stimulus CS^+^ _P_ —than for the other stimulus conditions. Thus, follow-up analyses will concentrate on the degree to which means differ by pre-exposure group and stimulus type for each trial using a Bonferonni-adjusted alpha, as well as examining plots of the mean response by stimulus type and trial for each pre-exposure group.

Hypothesis 3: Greater pain sensitivity will be associated with increased engagement of the proposed mechanisms of expected relevance and attention and increased LI.

To test the Hypothesis 3, pain sensitivity scores will be entered in the above analyses as a moderating variable. This will be done by testing interactions between pre-exposure and pain sensitivity.

Hypothesis 1b: Spaced pre-exposure sessions, compared to no spacing, will enhance LI of conditioned fear acquisition, recall, and retention. Hypothesis 2b: Pre-exposure in multiple contexts, as compared to pre-exposure in a single context, will enhance LI of conditioned fear acquisition, recall, and retention.

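### The test named for Hypothesis 3 (group by pain sensitivity, on the mediators only) leaves its latent-inhibition half untested and asks a different question of the mediator half

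*Protocol article*

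**What the plan says.** All references are to the protocol article.

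- **Hypothesis** (Research hypotheses; repeated in the same words in the Data analysis plan): "Greater pain sensitivity will be associated with increased engagement of the proposed mechanisms of expected relevance and attention and increased LI".
- **Lead-in to the hypotheses** (Research hypotheses): "Pain sensitivity will also be measured to test if this variable moderates the influence of the proposed mediators on LI".
- **Test** (Data analysis plan): "pain sensitivity scores will be entered in the above analyses as a moderating variable", followed by "This will be done by testing interactions between pre-exposure and pain sensitivity".
- **Models standing above that sentence**: the pre-exposure-phase MANOVA, which "will be run separately for the expected relevance and attention variables"; and, for conditioning, "we will conduct a three-way repeated measures MANOVA separately for the two proposed mechanisms".
- **Software** (Data analysis plan): Hypothesis 3 is grouped with 1a and 2a in SPSS. The remaining hypotheses, 1b and 2b, go to Mplus. Fear outcomes appear only in those Mplus mediation models, and no pain term is described there.
- **Groups** (Task phases and manipulations, with Table 2): every group has twelve pre-exposure trials. The groups differ only in how those trials are spaced and in which contexts they occur.

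**The concern.** The hypothesis is about an association: more pain sensitivity, more engagement, more LI. The planned test is about effect modification: whether differences between the four pre-exposure groups depend on pain sensitivity. The lead-in describes effect modification on another path, from mediator to LI. The three can all be true together, but one test cannot serve all three, and the one named is not the test of the hypothesis as worded.

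Two consequences follow. The Discussion presents the role of pain sensitivity in the LI of dental fear as a feature of the study, yet the stated models yield no result with a fear outcome. For the mediators, a non-significant interaction could be reported as failure of Hypothesis 3 when it is true, and a significant one as support when pain sensitivity matters in only one group.

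**Working it through.** **Step 1. Outcomes.** Set the two clauses of Hypothesis 3 against the models that contain pain sensitivity.

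| Clause or statement | Quantity needed | Model in the plan that contains it |
|---|---|---|
| More mediator engagement | pain effect on expected relevance and attention | SPSS MANOVAs; the only pain term named is pain by group |
| More LI | pain effect on the CS+NP versus CS+P difference in fear | none |
| Lead-in: moderates mediator-to-LI path | mediator by pain effect on fear | none |

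Reading LI as shorthand for the mediators does not work: Hypotheses 1 and 2 each separate part (a), the mechanisms, from part (b), LI of conditioned fear.

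**Step 2. Meaning of pre-exposure in the named interaction.** The Data analysis plan later speaks of the pre-exposure variable interacting with stimulus type. It is therefore the four-level group factor and not the CS+P/CS+NP contrast. With twelve trials in every group, that factor compares kinds of pre-exposure. The only comparator without pre-exposure is the within-subject stimulus CS+NP. The rationale in the Introduction, that traits which raise attention during pre-exposure should strengthen LI, predicts a pain effect inside every group.

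**Step 3. The plan's own figures.** Study participants gives no figure for Hypothesis 3; the sample size is stated to rest on Hypotheses 1 and 2. Those figures reproduce where checked:
- Mediation: n = (1.960 + 0.842)² × (1 − 0.3²) / [0.3² × (1 − 0.5²)] = 7.849 × 0.91 / 0.0675 = 105.8, so 106, as stated.
- Test phase: 134 is obtained for a repeated-measures MANOVA interaction with 4 groups, 4 trials and *f* = 0.20.

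Neither calculation contains a pain term.

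**Step 4. What the named interaction can detect.** Inputs: N = 180 from the protocol; equal groups of 45 (assumption); one standardised score per participant in place of the full repeated-measures model (simplification); group means 0, 0.3, 0.3 and 0.6 (assumption); pain slopes as shown (assumption). There were 4,000 simulated trials per row. The interaction is the 3-df group by pain test; the direct test is the common pain slope adjusted for group.

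| Truth | Group by pain significant | Direct pain slope significant |
|---|---|---|
| slope 0.3 in all four groups | 5.0% | 98% |
| slope 0.2 in all four groups | 5.5% | 77% |
| slope 0.4 in the focal group, 0 in the other three | 44% | 25% |

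Analytic check of the direct test: noncentrality = N r²/(1 − r²). For r = 0.3 this is 180 × 0.09/0.91 = 17.8, giving power 0.99. For r = 0.2 it is 180 × 0.04/0.96 = 7.5, giving power 0.78. With equal slopes the interaction's noncentrality is zero, so it rejects at the type I error rate whatever the sample size. In the last row the slopes average 0.1, and the interaction's noncentrality is 45 × (0.3² + 3 × 0.1²) = 5.4, giving power 0.46, close to the simulated 44%.

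**The case against.** **The mediator half may be testable in the same models.** This stands. A continuous variable entered in a repeated-measures model can yield pain by trial and, in conditioning, pain by stimulus, and CS+NP is there as a comparator. A reader might infer that these MANOVAs cannot address Hypothesis 3 at all; that is too strong. They can address the mediator half, but the plan names another term as the test. No such rescue exists for the LI half, because no fear measure is an outcome in those models.

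**The three statements might be called incompatible.** They are not. They are different quantities that could all hold, and Hypothesis 3 itself is worded identically in both places.

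**Hypothesis 3 was never presented as powered.** True, and the point does not depend on it. The mismatch is in what is tested; with equal slopes, more participants would not help.

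**The questionnaires.** Self-reported pain sensitivity comes from an adult form and, "with the Fear of Pain Questionnaire, Child report, in individuals from 6 to 17 years old", a child form. A reader might infer that combining them would create a spurious moderation effect. The documents do not support this. Nowhere does the article say that raw scores are pooled, and scoring can be left to an analysis plan. Groups are randomised, so age and instrument are independent of group in expectation. Simulated with raw scales offset by 0.5, 1 or 2 SD between instruments, half the sample under 18, age groups 0.5 SD apart on the outcome and no true pain effect (all assumptions), the group by pain test rejected in 4.7%, 4.5% and 4.8% of 4,000 runs. Age and instrument could distort a direct pain association, so the matter is relevant only as a safeguard for the corrected tests.

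**Conclusion.** The point holds as an error in the stated test of one of the three hypotheses. That the LI clause has no test follows from the text alone and needs no assumption. That the named interaction answers another question follows from all groups receiving twelve pre-exposure trials and from the plan's use of pre-exposure for the group factor.

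The size of the second part depends on how pain sensitivity acts. With a common slope the named interaction rejects at about 5%, while a direct test at N = 180 has about 98% power for a slope of 0.3 and 77% for 0.2. If the slope differs between groups, the interaction has some power, but for a claim that Hypothesis 3 does not make. The slopes are illustrative; the article gives none. The simulation uses a single summary score, so its percentages illustrate the contrast and do not forecast the power of the full MANOVA.

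**What to change.** 1. State Hypothesis 3 once, as one estimand, and bring the lead-in into line with it.
2. Name the deciding terms: pain by trial on expected relevance and attention in the pre-exposure phase; pain by stimulus (CS+P versus CS+NP) on the two mediators in conditioning; and pain by stimulus on the fear measures in conditioning, recall and retention.
3. Keep pain by group as a secondary question about who benefits from spacing or context change.
4. If moderation of the mediator-to-LI path is intended, add a mediator by pain term to the Mplus models.
5. For these association tests only, standardise the self-report score within the child and the adult questionnaire and adjust for age group.

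The cost is analysis-plan wording and a few more models. Every measure needed is already planned, so no visit, instrument or participant is added. The one downside is in item 5: standardising within instrument removes any true child/adult difference in pain sensitivity from the score.

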It may be possible to strategically leverage the LI effect to help prevent the formation of dental phobia. To design effective interventions, however, it is critical to understand the mechanisms underlying LI of dental fear. This knowledge would allow for the creation of maximally efficient LI interventions—ones that generate clinically meaningful effects. As such, our team initiated a program of research to clarify the mechanisms underlying the LI of dental fear in humans. This work is grounded in the Hall and Rodríguez model of LI [18], which proposes expected relevance (i.e., prediction errors) and attention as mechanisms responsible for LI. According to this model, novel stimuli have high informational value and as such, they attract attention. When a novel stimulus is presented without an unconditioned stimulus (UCS), the heightened attention increases the likelihood the individual will learn a “stimulus → no event” association. When exposure to the stimulus continues without a UCS, the individual is said to receive further evidence for this stimulus → no event association. Over time, one learns that the pre-exposed stimulus is a signal with little informational value, and attention is therefore diverted elsewhere. When the stimulus is later paired with a UCS, the lack of attention hampers the associability potential of that pre-exposed stimulus, thereby resulting in LI.

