## Methods

### Study participants

Participants will be 180 community volunteers between the age of 6 and 35, with this sample size based on an a priori power analysis for Hypotheses 1 and 2. The power analyses for Hypotheses 1a and 2a were focused on the simple pre-exposure-by-trial interaction for the conditioning and test phases. For the conditioning phase, use of G*power indicated a sample size of 19 is needed to detect a large effect, as suggested by our pilot study, (*f* = 1.3, α = 0.05, power = 0.80) whereas a sample size of 134 is needed for a given test phase to detect a small-to-moderate interaction (*f* = 0.20, α = 0.05, power = 0.80), where no prior effect size was available. For Hypotheses 1b and 2b, PASS software [24] indicated that a sample size of 106 is needed to achieve 0.80 power to detect an indirect effect equal to 0.15, where the standardized regression coefficient linking the mediator to the outcome is 0.3 and the correlation between the initiating variable and mediator is 0.5, with this correlation suggested by our pilot data.

Participants will be recruited in the regions surrounding the study sites in south Texas and northwest Ohio. It is expected that the study locations will provide the opportunity to recruit both Hispanic and African American participants, individuals that face increased burden from dental anxiety and poor oral health [11, 12]. Prior to entering the study, individuals will be screened using the inclusion/exclusion eligibility criteria displayed in Table 1. Participants will complete two or three in-person visits, depending on experimental condition, scheduled approximately 1 week apart. Participants will receive a $50 gift card for each visit. The Institutional Review Board of the primary institution approved the study.

**Table 1 Tab1:** Exclusion and inclusion criteria

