### Procedure

Individuals interested in the study will complete screening and screening consent on the phone or in a virtual meeting. Adults will screen for themselves, whereas a parent or legal authorized representative will screen for children and adolescents. Those qualifying after the screening of inclusion/exclusion factors will be scheduled for the first study session, with subsequent sessions occurring approximately one week apart from each other (min = 7 days). As described below, the number of sessions depends upon pre-exposure spacing condition.

At the start of session 1, participants will re-confirm eligibility, be provided a tablet device, and go through the informed consent (and assent, if appropriate) process. Parent or legal authorized guardian will provide permission for child and adolescent participants. Participants will then complete a pain sensitivity questionnaire and behavioral assessment of pain sensitivity, as described below. Researchers will then fabricate an individualized dental mouthpiece for the participant, place electrodermal activity electrodes on their hand, and deliver instructions for using the virtual reality set up. Using the randomization feature in REDCap (Research Electronic Data Capture; [25, 26]), participants will then be assigned to one of the four between-subject conditions. Randomization occurs during the first study visit, to maintain allocation concealment [27]. Participants will then begin the fear conditioning experimental task.

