To investigate Hypotheses 1b and 2b, we will conduct mediation analysis to estimate direct, indirect, and total effects associated with the pre-exposure groups on the distal outcomes of conditioned fear acquisition, recall, and retention. In parallel mediation models, the pre-exposure groups are hypothesized to impact the mediators (expected relevance and attention), which, in turn, are hypothesized to affect a given fear outcome. Note that these path models do not include within-subjects variables as the scores for the mediating variables will be obtained from the first trial of the conditioning phase, where stimulus group differences are expected to be greatest, and scores from a given distal outcome will be computed as the average of the scores across specific trials in the recall and then retention phase. If the pre-exposure variable is found to interact with stimulus type in Hypotheses 1a or 2a, then this model will be estimated separately for each stimulus type to assess if mediation is present for each stimulus.

Parameters for the mediation analyses will be estimated in Mplus with maximum likelihood estimation and percentile bootstrapping (with 20,000 bootstrap samples), with the latter used to test for the presence of indirect effects. Bootstrapping is a recommended method for mediation analysis given that indirect effects are non-normally distributed [37–39], as each indirect effect is computed as a *product* of parameter estimates.

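### The mediation models for Hypotheses 1b and 2b, as described, do not adjust the mediator-to-fear path for baseline pain sensitivity, which Hypothesis 3 links to both ends of that path

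*Protocol article*

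**What the plan says.** **Model.** In the Data analysis plan, Hypotheses 1b and 2b are addressed by parallel mediation models, fitted in Mplus, in which "the pre-exposure groups are hypothesized to impact the mediators (expected relevance and attention), which, in turn, are hypothesized to affect a given fear outcome". The mediator scores come from the first conditioning trial. The outcomes are averages over trials in the recall and then the retention phase. The only stated limit on content is this: "Note that these path models do not include within-subjects variables". No baseline covariate is mentioned.

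**Pain sensitivity as a hypothesis.** Hypothesis 3 reads: "Greater pain sensitivity will be associated with increased engagement of the proposed mechanisms of expected relevance and attention and increased LI". The opening of Research hypotheses gives a further aim: "Pain sensitivity will also be measured to test if this variable moderates the influence of the proposed mediators on LI".

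**Timing.** Under Procedure, in session 1 after consent and before the REDCap assignment: "Participants will then complete a pain sensitivity questionnaire and behavioral assessment of pain sensitivity, as described below".

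**Place in the analysis.** For Hypothesis 3, "pain sensitivity scores will be entered in the above analyses as a moderating variable", by testing pre-exposure-by-pain interactions. The analyses above that sentence are the Hypothesis 1a and 2a MANOVAs. Hypothesis 3 is assigned to SPSS; the mediation models come afterwards and are assigned to Mplus.

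**The concern.** Participants are randomised to a pre-exposure group, not to a level of expected relevance or attention. Randomisation therefore protects the group-to-mediator path and the total effect, but not the mediator-to-fear path. If pain sensitivity relates to the mediators and also to fear by another route, a model without it credits part of that shared variation to the mediator.

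The indirect effect is the product of the two paths, so the error passes straight into the quantity on which the mechanism claim rests. A pre-exposure-by-pain interaction in a MANOVA of the mediators does not adjust the mediator-to-fear path.

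There is also a mismatch within the document. The aim of testing whether pain sensitivity changes the mediators' influence on LI needs a mediator-by-pain term in a model for the fear outcome. The analysis plan describes no such term.

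**Working it through.** **Inputs from Study participants.** Group-mediator correlation a = 0.5; standardised mediator-outcome coefficient b = 0.3; indirect effect 0.15; power 0.80; required N = 106; planned N = 180. Two-sided alpha of 0.05 is stated for the G*Power calculations and assumed here for the mediation calculation.

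**Inputs not in the document (assumed).** Pain sensitivity has standardised effect p on the mediator and the same effect p, with the same sign, on fear: p = 0.1, 0.2, 0.3, 0.4. All variables have unit variance.

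**1. The plan's own figure.** n = (1.960 + 0.842)² × (1 − b²) / [b²(1 − a²)] = 7.849 × 0.91 / (0.09 × 0.75) = 105.8, so 106. The figure reproduces. It treats b as unconfounded.

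**2. Bias with one mediator.** Omitting pain sensitivity adds p²/(1 − a²) = p²/0.75 to b, and a times that to the indirect effect.

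| p | bias in b | bias in indirect effect | share of 0.15 |
|---|---|---|---|
| 0.1 | 0.013 | 0.007 | 4% |
| 0.2 | 0.053 | 0.027 | 18% |
| 0.3 | 0.120 | 0.060 | 40% |
| 0.4 | 0.213 | 0.107 | 71% |

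**3. False positives with one mediator, true b = 0.** The standard error is about 1/√(180 × 0.75) = 0.0861. At p = 0.3 the expected z is 0.120/0.0861 = 1.39, so the two-sided rejection rate is about 29%. At 0.1, 0.2 and 0.4 the rates are about 5%, 9.5% and 70%. A small percentile-bootstrap simulation of the indirect effect (400 replicates per setting) gave 15%, 28% and 70% at 0.2, 0.3 and 0.4. It gave about 8% with no confounding and 6% to 8% with pain sensitivity in the model.

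**4. Two parallel mediators, as planned.** Suppose pain acts on both mediators and they are otherwise independent given group. Each mediator then has conditional variance 0.75, and their covariance is p². Each spurious coefficient is p²/(0.75 + p²): 0.051, 0.107 and 0.176 at 0.2, 0.3 and 0.4. Simulation at N = 180 gives per-path rejection of about 9%, 23% and 51%; a normal approximation gives 9%, 24% and 54%. At 0.1 the rate is about 5%. The chance that at least one of the two paths is falsely significant is about 17%, 42% and 81%. With pain sensitivity in the model, the per-path rate returns to about 5%.

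**5. When mediation is real.** With true b = 0.3 and p = 0.3, the simulated unadjusted indirect effect averages 0.21 against a true 0.15; the adjusted estimate averages 0.149.

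**6. Sample size after adjustment.** Replace 1 − a² in step 1 by 1 − a² − p². At p = 0.4: 7.849 × 0.91 / (0.09 × 0.59) = 134.5, so 135. At 0.1, 0.2 and 0.3 the result is 108, 112 and 121.

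**The case against.** **Silence in an article.** The text excludes only within-subject variables, and a full plan could list covariates for the path models. So a reader should not infer that the plan forbids adjustment. What remains is that the document gives pain sensitivity a different job, in a different analysis and software, and states a moderation aim that the described models cannot test. That is more than brevity.

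**Cause or association.** A reader might infer that Hypothesis 3 says pain sensitivity drives mediators and fear. It says only that they are associated, and the assigned role is moderator. The confounding is therefore possible, not established.

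**Sign.** The Introduction argues that traits rousing more attention during pre-exposure should strengthen LI. If that extra attention lasted to the first conditioning trial, it would go with less fear, and the bias on the attention path would be negative. Inflation in favour of the hypothesis is one case, not the only one.

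**Size.** The coefficients are assumed, and at 0.1 the effect is negligible. The single-mediator figures overstate the per-path error of the planned model. If the mediators also correlate 0.4 given group (assumed), the per-path rates fall to about 6%, 14% and 38%. The chance that either path is falsely significant stays high, at 28% to 43% when p = 0.3.

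**Age and site.** The sample is "community volunteers between the age of 6 and 35" from two regions, and a reader might add both as known common causes. The document nowhere says that either affects the mediators or fear.

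**Parallel form.** The Introduction says that, once a stimulus carries little information, "attention is therefore diverted elsewhere", so a reader might conclude that only a serial model is correct. The document also names both variables as mechanisms, and both are scored on the same trial, so their order cannot be established from those scores. The parallel form is a defensible choice.

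**Conclusion.** The concern holds in a limited form. As described, the Hypothesis 1b and 2b models leave the non-randomised mediator-to-fear path unadjusted for a pre-randomisation variable that the plan itself expects to be related to both the mediators and LI. The stated aim of testing moderation of the mediators' influence has no matching analysis.

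The consequence ranges from nothing noticeable (pain effects of 0.1) to a per-path false-positive rate of about one half (0.4, two mediators otherwise independent given group). This rests on equal, same-sign, assumed effects, and the direction could differ. The total effect of group on fear and the group-to-mediator effects are not touched. The document does not support calling the indirect effects invalid outright.

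**What to change.** State in the analysis plan, before outcome data are examined, that every path model includes baseline pain sensitivity as a covariate in both the mediator and the outcome equations. Use the cold pressor score and the questionnaire score, the latter standardised within the adult and the child instrument because the two age groups complete different forms. Add mediator-by-pain terms to the outcome equation so that the stated moderation aim is tested. Report a sensitivity analysis for residual mediator-outcome confounding, because one measured covariate does not remove the unmeasured ones.

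Do not use scores from the first six pre-exposure trials as a baseline covariate. They follow randomisation, and some multiple-context participants start in the green environment while single-context participants start in the tan one, so those scores can depend on assigned group.

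Cost: both pain measures are already collected, so this needs analysis wording, some rescaling, a few degrees of freedom and slightly wider intervals. The required N rises from 106 to at most about 135 at the values above, below the planned 180. That figure covers adjustment for one pain score in a single-mediator model; it is not a power statement for the interaction terms.
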